## Abstract

The anatomy of the upper airways influences the risk of obstructive sleep apnea (OSA). The size of soft tissue structures, such as the tongue, soft palate, and lateral walls of the pharynx, contributes to the pathogenesis of OSA. New lines of treatment for sleep apnea, such as myofunctional therapy (MT), aim to strengthen the oropharyngeal musculature to improve the defining parameters of apnea. The present protocol uses ultrasound imaging to measure the size of the lingual musculature non-invasively and cost-effectively and evaluates the changes in its morphology. Eligible patients include those with OSA who have undergone submental cervical ultrasound and drug-induced sleep endoscopy before starting MT with the AirwayGym app. Follow-up evaluations are conducted at 3 months after beginning treatment. Patients diagnosed with OSA via questionnaires and polysomnography or respiratory polygraphy are evaluated anatomically and functionally using the Iowa Oral Performance Instrument, a tongue digital spoon, somnoscopy, and submental cervical ultrasound to assess their responses to the AirwayGym app. The lingual thickness (mm) and volume (cm^3^) and the distance between both lingual arteries (mm) are measured. The AirwayGym app helps users and therapists monitor the patient performance of MT. Incorporating submental ultrasound can be a useful non-invasive tool to evaluate OSA and MT.

## 1. Introduction

Obstructive sleep apnea (OSA) is one of the most predominant respiratory diseases affecting 6–9% of women, 6–20% of men in middle ages, and 1–3% of children. Higher body mass index (BMI), agedness, and male sex are the most significant risk factors [1,2,3].

The anatomy of the upper airways also influences the risk of OSA, and the size of soft tissue structures, such as the tongue, soft palate, and lateral walls of the pharynx, contributes to the pathogenesis of OSA [4,5].

Different etiologies suggested to explain OSA include a reduced muscular genioglossus tone, low hypoglossal nerve activity not allowing the pharyngeal muscle to keep an open airway, anatomical factors like tonsils and adenoid hypertrophy, cephalometric alterations such as mandibular and hyoid bone position and the length of the soft palate, obesity and neck fat, a low respiratory arousal threshold, and, finally, alterations in the ventilatory control drive “loop gain” [6]. Some authors have suggested that the main reason for this disease is the malfunctioning of the genioglossus muscle, which is the main upper airway’s dilating muscle [6,7].

Magnetic resonance imaging (MRI) can provide a detailed characterization of the tongue, including its fat content, which has been shown to correlate with the severity of OSA [8,9]. Reducing tongue fat has been demonstrated a key factor in improving the apnea–hypopnea index (AHI) in OSA patients [9]. New lines of treatment for this disease, such as myofunctional therapy (MT), aim to strengthen the oropharyngeal musculature to improve the defining parameters of apnea, such as snoring, daytime sleepiness, AHI, and values on the Iowa Oral Performance Instrument (IOPI) for sensorimotor issues [10,11,12].

Floppy structures involving the upper airways appear to result in a narrow and collapsible airway. However, the effects of parapharyngeal fat deposits at different levels on the severity of OSA are not clear. Drug-induced sleep endoscopy provides three-dimensional and dynamic evaluations of upper airway collapse under conditions that better approximate natural sleep than with an awake patient [13].

MRI is the most commonly used imaging method to measure volumes and obstruction in the upper airways. Recent studies have incorporated computed tomography with the patient under sedation [14] and ultrasound. Ultrasound is a non-invasive, low-risk, and cost-effective imaging modality that can also be used to assess the tongue. Submental ultrasound can be used to characterize the tongue in patients with OSA and has shown that an increased width and thickness of the tongue are associated with severe OSA [15,16]. Ultrasound can also be used to examine the dynamic movements that characterize changes in tongue morphology with activities such as the Müller maneuver [17,18]. Yu et al. [19] reported that the ultrasound echo intensity increases with increasing fat content in the tongue and strongly correlates with tongue fat measurements in MRI.

In the context of OSA, submental ultrasound can be used to determine whether the size of the tongue muscles is adequate to keep the upper airways open during sleep. Small or weak muscles may increase the risk of airway obstruction and sleep apnea [20]. MT can increase the size and strength of the genioglossus and geniohyoid muscles, which helps to improve upper airway function and reduce the severity of OSA.

Myofunctional therapy (MT) is based on oropharyngeal exercises that try to obtain a proper tongue positioning in the oral cavity. Guimaraes [21] in his randomized clinical trial (RCT) demonstrated that oropharyngeal exercises reduced the OSAS severity from an apnea–hypopnea index (AHI) of 22.4 +/− 4.8 to 3.7 +/− 8.5 events/hour. MT is composed of isotonic and isometric exercises that target oral structures (i.e., the lips and tongue) and oropharyngeal structures (i.e., the soft palate and lateral pharyngeal wall). There has been an increasing number of studies evaluating the effect of MT in the form of case studies, case series, and, most recently, two RCTs [12,22,23,24,25,26]. Because MT raises serious concerns relating to adherence, our sleep unit has designed the AirwayGym app to perform these exercises.

Using this protocol, we can examine the usefulness of ultrasound in predicting the treatment response to MT delivered by specialists using the AirwayGym application employed in our sleep unit.

The AirwayGym application was created in 2018 by the Sleep Units of the Quiron Salud Marbella and Campo de Gibraltar Hospital together with the computer engineering departments and developed by the apnea company Bye.

The novelty of this application is that the patient carries out his therapy from home with his smartphone, providing him with feedback on the effectiveness of the exercises that can also be supervised by his therapist. Complete information about the application is provided at https://airwaygym.App/ (accessed on 27 January 2024). Every therapist can sign up and track their patients [27].

The objective is to conduct a prospective, non-randomized pilot study in patients with moderate–severe obstructive sleep apnea–hypopnea syndrome (OSAS).

We measure with ultrasound the thickness of the lingual and pharyngeal walls, the distance between both lingual arteries, and the height and lingual volume in the patients included in this study.

The desired impact is to improve adherence to CPAP and myofunctional therapy, as well as perform simple anatomic evaluations such as ultrasound. If this improves treatment adherence and can diagnose and treat these patients in the future, there is ample scope for further clinical trials.

## 2. Experimental Design

This is a nonsponsored prospective, non-randomized pilot study coordinated by the Pulmonology, Anesthesiology, and Otolaryngology Departments of Quirónsalud Marbella Hospital and Campo de Gibraltar Hospital, Andalucia, Spain. This study has been registered (ISRCTN92645461) and approved by the local ethics committee (AWGAP20232).

### 2.1. Study Population

This study will include patients diagnosed with sleep apnea–hypopnea at the participating centers and who agree to participate in this study.

### 2.2. Study Groups

The control group will include patients with recent moderate–severe sleep apnea (1–3 months) undergoing treatment with continuous positive airway pressure (CPAP) therapy. An initial ultrasound measurement of the tongue genioglossus fat will be made and 3 months after inclusion in this study.

The MT group will include patients with moderate apnea. MT exercises alone, once a day for 3 months, will be performed exclusively via the AirwayGym app. An initial ultrasound measurement and drug-induced sleep endoscopy (DISE) will be performed with repeated control at 3 months.

In the MT-CPAP severe apnea group, patients will use CPAP at night, measuring the number of hours they use it at night. A new sleep study will be performed at 3 months. An initial ultrasound measurement and DISE will be made with control at 3 months (Figure 1).

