The distribution of visits to the center will be as follows:Pulmonology visit: Patients will be diagnosed with OSA in a pulmonology laboratory via an initial sleep study, which includes the measurement of baseline AHI, the nocturnal desaturation index, and the lowest oxygen saturation levels during the night.Otorhinolaryngology visit: Patients will be assessed by the otorhinolaryngologist, who will evaluate the anatomy and functionality of the upper airways using DISE and measure tongue strength with the IOPI and TDS. The AirwayGym app is recommended for patients with oropharyngeal hypotonia.Ultrasound visit: A neck ultrasound will be performed to measure tongue thickness (mm), height (mm), volume (cm^3^), and distance between the lingual arteries (mm) before DISE and at the start of treatment modulation with the app (Figure 4 and Figure 5).Monthly telemedicine follow-up: During the 3-month study period, all patients in the three groups will be monitored for adherence and incidents related to the prescribed treatment with the AirwayGym app.Three-month follow-up: All variables evaluated during the initial visit will be measured again after three months. The ultrasound visit is an evaluation added to this previously published protocol (Tongue +) [36]. A submental ultrasound will be performed in the context of sleep apnea.

The Kolmogorov–Smirnov test will be used for the distribution of quantitative variables. The chi-square test or Fisher test will be used as necessary for the study of categorical variables. Student’s *t*-test or ANOVA (for two or more samples) will be used to study the differences between quantitative variables.

Non-parametric tests (Mann–Whitney or Kruskal–Wallis) will be used if the variables to be analyzed do not follow a normal distribution. The level of statistical significance will be set at *p* < 0.

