### 5.1. Preliminary Results

Additionally, submental ultrasound may be useful to evaluate the effectiveness of MT in sleep apnea. Studies have shown that myofunctional therapy can increase the size and strength of the genioglossus and geniohyoid muscles, which can improve upper airway function and reduce sleep apnea. Submental ultrasound can be used to measure these muscle changes and evaluate the effectiveness of therapy. With 10% of the patients included, there were significant differences (*p* < 0.05) in the initial volume (mm^3^) and lingual thickness (mm) between the control patients and the patients in the groups with moderate–severe sleep apnea. After 3 months of myofunctional therapy, we found a statistically significant improvement in the values of the functional examination with IOPI and the digital spoon and a reduction in lingual thickness (mm) of >15% in the patients studied.

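### Group membership ties myofunctional therapy to apnoea severity and CPAP, so the unadjusted between-group tests do not isolate its effect unless every control is severe

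*Protocol article*

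**What the plan says.** All references are to the protocol article.

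- **Design (section 2):** "This is a nonsponsored prospective, non-randomized pilot study".
- **Groups (section 2.2):** controls are "patients with recent moderate–severe sleep apnea (1–3 months) undergoing treatment with continuous positive airway pressure (CPAP) therapy". For the MT group, "The MT group will include patients with moderate apnea" and "MT exercises alone, once a day for 3 months, will be performed exclusively via the AirwayGym app". For the third group, "In the MT-CPAP severe apnea group, patients will use CPAP at night"; its name shows that it also receives MT.
- **Size (section 4.1):** 15 patients per group, as a pilot.
- **Severity bands (section 4.3):** moderate is AHI 15 to 29.9 and severe is AHI 30 or more.
- **Prior treatment (section 4, inclusion criteria):** as the criterion reads, controls may have had up to 3 months of earlier treatment. The other groups have no such allowance.
- **Aim (section 2.3):** the first objective is the influence of MT on cervical fat and ultrasound parameters.
- **Tests (end of section 4.3):** Student's t-test or ANOVA ("for two or more samples) will be used to study the differences between quantitative variables"), with Mann–Whitney or Kruskal–Wallis for non-normal variables. No covariate, stratum or matching is mentioned.
- **Limitations (section 5.2):** small numbers, few controls and no blinding. Confounding by severity or CPAP is not named.

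**The concern.** The first objective asks a causal question about MT, but a patient's group is set by severity, and CPAP use follows the group. The article itself links severity to the outcomes. The Introduction says that tongue fat correlates with the severity of apnoea and that greater tongue width and thickness go with severe disease. Groups with different severity mixes can therefore be expected to differ on the ultrasound measures without any effect of MT.

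If the listed tests are read as tests of MT, a difference at 3 months could be credited to MT when it comes from severity or CPAP. A real MT effect could equally be masked.

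**Working it through.** The article gives no effect size, SD or power behind 15 per group, so it has no figure to reproduce. The check has three parts.

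**1. What each contrast contains.** Let s be the share of controls with severe apnoea. It is not stated and can lie anywhere from 0 to 1. Assume additive effects.

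| Group | MT | CPAP | Severe share |
|---|---|---|---|
| Control | 0 | 1 | s |
| MT | 1 | 0 | 0 |
| MT-CPAP | 1 | 1 | 1 |

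Subtracting rows gives:

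- MT − control = MT effect − CPAP effect − s × severity effect
- MT-CPAP − control = MT effect + (1 − s) × severity effect
- MT-CPAP − MT = CPAP effect + severity effect (the MT term cancels)
- Mean of the two MT groups − control = MT effect − 0.5 × CPAP effect + (0.5 − s) × severity effect

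Three group means face four unknowns: intercept, MT, CPAP and severity. The design matrix has rank 3. The MT effect is not estimable at s = 0, 0.25, 0.5 or 0.75. At s = 1 it is estimable, because MT-CPAP − control then reduces to the MT effect.

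**2. Illustration of the size.** This is a simulation with 40,000 replicates, 15 per group and unit-variance normal outcomes. The true MT and CPAP effects are both zero. Three inputs are assumptions:

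- Severity shifts the analysed variable by 0.5 or 1.0 SD.
- The number of severe controls is 4, 8 or 10 of 15.
- The test level is two-sided 0.05, because the level printed in section 4.3 is cut off.

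| Severe controls | Severity effect | MT vs control | MT-CPAP vs control | Three-group ANOVA |
|---|---|---|---|---|
| 4 of 15 | 0.5 SD | 5.9% | 15.7% | 20.8% |
| 4 of 15 | 1.0 SD | 9.1% | 45.3% | 65.5% |
| 8 of 15 | 0.5 SD | 10.3% | 8.9% | 19.1% |
| 8 of 15 | 1.0 SD | 25.1% | 20.2% | 61.4% |
| 10 of 15 | 0.5 SD | 13.6% | 7.0% | 20.1% |
| 10 of 15 | 1.0 SD | 37.7% | 12.0% | 63.2% |

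The entries are rejection rates with no MT effect present. The two pairwise contrasts move in opposite directions as the severe share rises, as the formulas predict.

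**3. Precision of the one usable contrast.** The difference detectable with 80% power at two-sided 0.05 (normal approximation) is d = (1.960 + 0.842) × √(1/15 + 1/n), where n is the number of controls used. Rounding up to 0.01:

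- n = 15: 2.802 × 0.365 gives d ≈ 1.03 SD
- n = 8: 2.802 × 0.438 gives d ≈ 1.23 SD
- n = 7: 2.802 × 0.458 gives d ≈ 1.29 SD

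The values 7 and 8 assume that about half the controls are severe.

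**The case against.** **It is an openly non-randomized pilot, and the test list is generic.** The article names no pairwise contrast and does not say whether 3-month values or changes are compared. A fuller plan may add adjustment. This stands as a reason for moderation. It does not remove the point, because the confounding lies in the printed group definitions and no choice among unadjusted contrasts escapes it.

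**The usable comparison may already exist in the data.** Controls can include severe patients on CPAP, and the limitations paragraph suggests severe patients among them. This also stands. It is why analysis and reporting can repair much of the problem, but the article neither requires severe controls nor names that comparison.

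Three stronger readings are tempting and are not supported:

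- *Baseline imbalance is proven.* Section 5.1 reports early differences in initial lingual volume and "lingual thickness (mm) between the control patients and the patients in the groups with moderate–severe sleep apnea". That rests on 10% of patients (about 4 or 5 of 45). It also sets controls against groups with moderate–severe apnoea, although the section 2.2 controls are themselves moderate–severe. It is weak support only.
- *MT patients are selected for hypotonia.* Section 4.3 says "The AirwayGym app is recommended for patients with oropharyngeal hypotonia". That is a recommendation at a visit, and hypotonia is not an eligibility criterion for any group.
- *The non-overlapping AHI bands, or regression to the mean in AHI, measure the bias.* Both bear on MT-CPAP versus MT. Both of those groups receive MT, so that comparison says nothing about the MT effect.

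**Conclusion.** The point holds and should be fixed before analysis; the pilot label and the open lack of randomization keep it below a must-fix. No unadjusted between-group comparison identifies the MT effect unless all controls are severe. That conclusion follows from the group definitions and additive effects alone.

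The false-positive rates (6–38%, 7–45% and 19–66% for the three tests) depend on the assumed severity effect and severe share. They show direction and range, and are not estimates for this trial.

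A reader might infer that the study can say nothing about MT. That goes too far. MT-CPAP against CPAP controls, adjusted for the baseline value and AHI, is informative within the limits of a non-randomized comparison.

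**What to change.** 1. Make MT-CPAP versus CPAP controls the only between-group MT contrast. Analyse the 3-month ultrasound or strength value by ANCOVA with its baseline value and baseline AHI as covariates. Add few or no others at about 15 per group.
2. Report controls by severity, with the severe-control subset as a supporting analysis. The AHI adjustment assumes a common slope and no interaction of MT with severity. Controls below AHI 30 have no counterpart in the MT-CPAP group, so the subset shows how far the result leans on that assumption.
3. Report MT alone as a single-arm before-after estimate, and say that it does not separate MT from time or regression to the mean. Do not interpret the three-group ANOVA or Kruskal–Wallis test as a test of MT.
4. Add residual confounding by severity and by controls' earlier CPAP to the limitations. Adjusting for time on CPAP would not help, because the inclusion criteria make it nearly a marker of group.
5. Reconcile section 2.2, where controls are on CPAP, with section 5.2, which explains the halt in control enrolment by the difficulties of severe patients without appropriate therapy. Because enrolment was stopped, the fix relies on controls already recruited.

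**Cost:** analysis and reporting text only. Initial AHI is already a listed variable, and section 4.3 has the initial measurements repeated at three months. The downside is precision: before covariate adjustment, the detectable difference is about 1.03 SD with all 15 controls and about 1.2 to 1.3 SD if only 7 or 8 are severe. The claim about MT also becomes more modest.

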### 2.3. Objectives

-To evaluate the influence of MT on the reduction in cervical fat and the improvement of ultrasound parameters in sleep apnea.-To measure different parameters related to the function and size of the genioglossus and geniohyoid muscles to evaluate the presence and severity of sleep apnea, as well as the effectiveness of myofunctional therapy in improving the function of these muscles.-To determine whether performing a neck ultrasound is relevant for the indication of TM in sleep apnea.-To evaluate whether performing ultrasound and DISE modify the indication of surgical techniques compared with if we only performed DISE.-To evaluate the adherence to CPAP and MT.

The hypothesis of our work is based on determining whether knowledge of the fatty and muscular components can be decisive in the choice of pharyngoplasty techniques, in multilevel surgery, and as a possible predictor of response or failure to MT since, currently, the influence that TM can have on reducing cervical fat is unknown.

Given that the aforementioned tools only measure strength, we consider the previous study of cervical fat using ultrasound and its response to TM relevant in the study of collapse patterns during DISE.

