### 4.2. Definition of Variables

The variables that we will measure in all patients and that are reflected in the data collection table using IBM SPSS Statistics version 28 with Windows software are as follows:Age;Sex;Weight;Height;BMI;Abdominal circumference (at the level of the navel);Neck circumference (with a flexible tape on the most prominent part; for this, it is necessary for the patient to be standing, with arms hanging at the sides, head erect, and gaze forward);Measurement with IOPI of tongue force and buccinator muscle;Measurement with digital spoon (DS);Initial AHI;Ranking of velum, oropharynx, tongue base, and epiglottis (VOTE) in DISE, before and after;Ultrasound measurements: echo intensity, tongue height (mm), and tongue width (mm).

To develop the protocol, patients with sleep apnea underwent submental cervical ultrasound and DISE before starting to use the AirwayGym app (www.airwaygym.app, accessed on 27 January 2024) and after 3 months of treatment.

The AirwayGym app is a portable fitness app (Figure 2) intended for patients rather than athletes, and therapists rather than coaches provide the instructions. The novelty of this app is that it is the first healthcare app on the market that allows patients to directly interact with a smartphone without the need for any other device. The app focuses on improving proprioceptive deficits in patients with sleep apnea. When used with the app, the smartphone provides acoustic feedback on the effectiveness of the MT exercises performed [27].

The AirwayGym app comprises daily tension and concentration exercises (i.e., isometric and isotonic exercises, respectively) that can be performed anywhere. It offers the additional advantage of providing prompt feedback to allow patients to see their progress and resolve problems with the help of a therapist. Before each exercise, an animated demonstration and video provide instructions for performing the exercise. After each exercise, patients receive visual, acoustic, and tactile feedback as a score on the success of their performance. A chat function is available via which patients can contact the therapist directly. This app complies with regulations 2002/58/EC and (EU) 2016/679 regarding data protection. It is priced at EUR 8.99. Additional information can be found on the AirwayGym website.

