### 4.3. Assessments

Patients will be jointly evaluated by the pulmonology and otorhinolaryngology services of the hospital.

Evaluation by a pulmonology specialist: A detailed medical history is taken to record symptoms and risk factors associated with sleep apnea. BMI is calculated, and questionnaires that assess daytime sleepiness (the Epworth test; Appendix A) and sleep quality (the Pittsburgh questionnaire; Appendix B) are administered. Patients suspected of having sleep apnea undergo either polysomnography or diagnostic respiratory polygraphy based on their clinical symptoms. After this first assessment, the pulmonologist refers the patient to the otorhinolaryngology department to assess the anatomy and functionality of the upper airways. Patients with a BMI of >30 are transferred to the nutrition and dietetics unit. It is known that a reduction in BMI of 5–10% significantly reduces the AHI [32].

The sleep study is performed using standard polysomnography.

Standard nocturnal polysomnography involves (i) recordings of sleep-related electroencephalography (EEG), electromyography (EMG) of the chin and leg muscles, electrooculography (EOG), and electrocardiography (ECG); (ii) oxygen saturation; and (iii) measures of respiratory effort and airflow.

The tests are used to define PS with an AHI of <5 events/h of sleep, moderate OSAHS as an AHI of 15 to 29.9 events/h of sleep, and severe OSAHS as ≥30 events/h of sleep [eleven].

Laboratory-assisted polysomnography has been and continues to be a gold standard for the diagnosis of sleep-disordered breathing, although the usefulness of a single night-time recording for diagnosis can generate considerable variability in the AHI from night to night, especially when the AHI is low [11].

Therapy with the AirwayGym^®^ application will be initiated after inclusion in this study. This therapy will be applied to patients with an average duration of training of 5 days a week with 15–20 min/session. Three months after myofunctional therapy, an otorhinolaryngological evaluation, sleep questionnaires, and tongue strength measurements with the IOPI and ultrasound will be performed [11].

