Evaluation by an otorhinolaryngology specialist: The otorhinolaryngology specialist is responsible for the anatomical and functional examination of the upper airways. During this consultation, the Friedman stage and Müller maneuver are assessed, and nasofibrolaryngoscopy is performed to determine the degree of retropalatal and/or retrolingual collapse. Subsequently, functional evaluation is performed using the IOPI Medical Device to assess tongue strength by measuring the maximum pressure and tongue fatigue by measuring resistance. Low resistance values indicate a high tendency to fatigue, in which case patients would benefit from treatment modulation with the AirwayGym app.

Another instrument for measuring tongue tone is the tongue digital spoon (TDS), which has recently been applied for the diagnosis and evaluation of patients with sleep apnea and lingual hypotonia [33,34]. In addition to telemedicine follow-up, patients will be provided with a sleep diary for symptom control (Appendix C to evaluate the response and adherence to therapy with the AirwayGym app. After this consultation, the patient will be offered DISE and cervical ultrasound to optimize the selection of the current treatments for sleep apnea [35].

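### Objective 3: the plan cannot show whether neck ultrasound changes who is offered myofunctional therapy; it supports at most an exploratory look at response prediction

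*Protocol article*

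**What the plan says.** **Objective.** Section 2.3 of the protocol article lists "To determine whether performing a neck ultrasound is relevant for the indication of TM in sleep apnea". The next objective concerns surgery and is written as a comparison: "To evaluate whether performing ultrasound and DISE modify the indication of surgical techniques compared with if we only performed DISE".

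**Who gets MT.** Section 2.2 ties it to severity: "The MT group will include patients with moderate apnea", and "In the MT-CPAP severe apnea group, patients will use CPAP at night" in addition to MT. Controls have moderate to severe apnea and are on CPAP. In the visit list of section 4.3 another criterion appears, at the otorhinolaryngology visit: "The AirwayGym app is recommended for patients with oropharyngeal hypotonia". The same section says "Therapy with the AirwayGym^®^ application will be initiated after inclusion in this study".

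**Role of ultrasound.** Section 4.3 says that "the patient will be offered DISE and cervical ultrasound to optimize the selection of the current treatments for sleep apnea", but gives no threshold or rule. The ultrasound visit is listed after the otorhinolaryngology visit, and the scan is to precede drug-induced sleep endoscopy (DISE).

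**Data and analysis.** Section 4.2 includes "Ultrasound measurements: echo intensity, tongue height (mm), and tongue width (mm") among its variables, but no item for the MT indication. The end of section 4.3 names distribution checks, tests for categorical variables, and tests of differences between groups.

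**The concern.** An indication is a decision about who should be offered a treatment. To learn whether a test bears on that decision, one normally needs the decision as it stands without the test and again once the result is known. Here MT follows severity or hypotonia, and patients in the two MT groups receive it whatever the scan shows. A change in ultrasound measures over three months among treated patients describes the effect of time and treatment. It does not tell us whether the scan would have altered the offer of MT.

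The stake is the use made of the result. Section 4.3 offers ultrasound as an aid to choosing treatment, and the Discussion (section 5.2) expects muscle-pattern information to support better treatment decisions. Without a recorded decision, the trial would have nothing to back a claim that ultrasound belongs in the indication for MT.

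**Working it through.** The plan gives no figure for this objective, and the 15/15/15 size rests on no effect size or power, so there is nothing to reproduce. The check traces the objective through the plan and then sizes the two ways of addressing it.

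**Step 1. Trace.**

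| Element | Place | Does ultrasound enter? |
|---|---|---|
| MT by severity | 2.2 | No |
| MT recommended on hypotonia | 4.3, otorhinolaryngology visit | No; listed before the ultrasound visit |
| Start of MT | 4.3 | No; after inclusion |
| Ultrasound to help choose treatment | 4.3 | Yes, but no rule and no recorded decision |
| Variable list | 4.2 | Measurements only; no MT indication |
| Tests | 4.3 | Group differences only |

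No row yields an MT decision without ultrasound paired with one made with it. A later analysis plan could add a test, but it could not recover a decision that nobody wrote down before the scan.

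**Step 2. The response-prediction route.** The Introduction and the hypothesis in section 2.3 present ultrasound as a possible predictor of MT response. The available patients are 15 + 15 = 30. Assumed: two-sided alpha 0.05 and 80% power, so 1.960 + 0.842 = 2.802.

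- Smallest detectable correlation, tanh(2.802/√(n − 3)):
  - n = 30: tanh(2.802/5.196) = 0.49
  - n = 15 (one MT group): tanh(2.802/3.464) = 0.67
- Smallest detectable standardised difference in baseline ultrasound between responders and non-responders, 2.802 × √(1/n₁ + 1/n₂), with the split assumed:
  - 15 v 15: 2.802 × 0.365 = 1.02
  - 10 v 20: 2.802 × 0.387 = 1.09
- Power at a difference of 0.8 SD: 0.59 (15 v 15) or 0.54 (10 v 20).

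Three further limits apply:

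- Response is not defined.
- Regimen and severity coincide (moderate: MT alone; severe: MT with CPAP), so their effects cannot be separated.
- A three-month sleep study is stated outright only for the MT-CPAP group (section 2.2), although section 4.3 says that all initial variables are measured again.

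**Step 3. What a recorded decision would give.** The exact (Clopper-Pearson) upper 95% limit for zero changes in n patients is 1 − 0.025^(1/n).

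- n = 45: 1 − 0.025^(1/45) = 7.9%
- n = 30: 1 − 0.025^(1/30) = 11.6%

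For an illustrative 20% changed, the exact intervals are 9.6% to 34.6% (9 of 45) and 7.7% to 38.6% (6 of 30). These counts are examples, not forecasts.

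**The case against.** The strongest reply is that the objective asks whether ultrasound is relevant to the indication, not whether it modifies it. The with-and-without comparison is written only into the surgical objective. A baseline measure that predicts response or failure is also relevant to an indication, and the Introduction and section 2.3 state that route. A t-test or Mann-Whitney test from section 4.3 could compare baseline ultrasound between responders and non-responders. The Conclusions (section 6) call ultrasound a tool for evaluating apnea and responses to MT, which fits this reading.

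This stands in part. A reader might infer that the objective cannot be answered at all, or that no patient contributes any information to it. The documents do not support that, because 30 MT patients are to have ultrasound at baseline and at three months, and an exploratory prediction analysis is possible. Nor do the Conclusions promote ultrasound as a means of selecting patients. But prediction of response is not the same question as indication, and the plan does not yet define that analysis either.

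A second reply is that the list in section 4.2 is not exhaustive. It omits the sleepiness and sleep-quality questionnaires, tongue volume and CPAP hours, all planned elsewhere, and the article may condense a fuller protocol. So the missing item alone proves little. The point rests instead on the printed rules for giving MT and the order of visits, which leave ultrasound out of the decision.

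Third, a second yes/no given with the scan in view is unblinded opinion, with no ultrasound threshold behind it. That is right, and the result should be labelled accordingly.

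**Conclusion.** The point holds in a limited form. As printed, the plan cannot show whether neck ultrasound changes who is offered MT, because the offer is fixed by severity or hypotonia and no indication with and without the scan is described. What remains is an exploratory look at response prediction in 30 patients. It could detect only large associations (r of about 0.49, or a difference of about 1.0 to 1.1 SD), and its response definition and analysis are still open. Those sizes assume two-sided alpha 0.05, 80% power, complete follow-up and the responder splits shown. The conclusion about indication depends on none of them.

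Separately, the severity rule in section 2.2 and the hypotonia rule in section 4.3 are different grounds for giving MT, and the passages must be reconciled.

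**What to change.** **Option A, keep the indication question.** At the otorhinolaryngology visit, before the ultrasound, record 'MT indicated: yes/no' from history, IOPI and digital spoon. Record the same item after the ultrasound result is seen, without changing the patient's group or care. The first item should not depend on DISE, because section 4.3 puts ultrasound before DISE and section 2.2 states DISE only for the two MT groups. Report the proportion changed in each direction with an exact 95% interval, and call it exploratory because the second decision is unblinded and hypothetical. Include the controls if possible: if entry to the MT groups already requires an MT recommendation, those 30 patients can show changes in little more than one direction.

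**Option B, restate the objective.** Make it exploratory prediction of MT response, with response defined in advance and a named comparison of baseline ultrasound by response. Draw no conclusion about indication.

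Under either option, reconcile the two stated grounds for giving MT.

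**Cost.** Option A needs two form items and a fixed order of recording, with no added visit or procedure. Option B needs only text, but gives up the claim about indication.
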